### Participants

Adults with CKD stage 5 (from any cause), commencing in-centre maintenance HD therapy for end-stage renal disease (ESRD) in the out-patient settings. Full eligibility and exclusion criteria are presented in Table 1. Pre-dialysis specialist nephrology input for at least 3 months is essential since those without full preparation for dialysis may require intensive dialysis at presentation [22, 23] (i.e., unsuitable for incremental HD).

**Table 1 Tab1:** Eligibility criteria for study participants

Inclusion criteria	Exclusion criteria
Age ≥ 18 patients with CKD-5 who are about to start planned HD At least 3 months of prior specialist renal follow-up at the time of starting HD Able to meet all the study requirements Written signed informed consent	Age < 18 No prior contact with nephrologists for > 3 months Cross-over into HD from peritoneal dialysis Currently undergoing HD therapy Any condition which in the opinion of the investigator makes the participant unsuitable for entry into the study Participation in an interventional study in the preceding 6 weeks History of myocardial infarction in the preceding 3 months Inability to provide informed consent Inability to comply with the study schedule and follow-up

*CKD* chronic kidney disease, *HD* haemodialysis

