#### Recruitment for control arm (historical controls)

Each participant in the incremental HD arm of the study will be matched with 2 patients who had previously received the conventional HD treatment (historical controls; matching ratio 1:2). Participants for the control arm will be identified using the local dialysis treatment database. All patients starting HD therapy since 2013, the inception date of the database, will be included in the searches. Their dialysis treatment data (including nursing notes and exceptions), along with details of their medical history will be extracted for further analysis (see below).

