#### Safety and adverse events data

There are several safety measures built-in to our incremental HD program to protect patients from the deleterious effects of a rapid decline in RRF around the time of dialysis initiation or when at least three-times weekly dialysis is needed from the start. First, we are only recruiting patient with planned out-patient dialysis start; this excludes the majority of those who develop critical or life-threatening issues related to CKD-5. Furthermore, all participants are reviewed at the start (see study procedures in supplementary table S1) to ensure safety before patients commence the program. During the program, patients receive regular visits from the study team (in the first month, five study related checks are undertaken including review by the study medic on four occasions). Also, clinicians can change the dialysis schedule e.g., offer extra dialysis or to take the patient off the program completely at any point during the study; for this reason, the mid-week dialysis slot is always kept open in case a participant needs additional dialysis. Finally, this a short incremental regime lasting just over 3 months; hence, a decline in RRF is anticipated and treatment increases are pre-emptive in this program.

Information related to adverse events (AEs) and serious adverse events (SAEs) will be recorded continuously throughout the study based on definitions presented in supplementary table S2. Routinely, all dialysis treatments are recorded in the local dialysis treatment database and a named nurse documents a narrative account of that day’s treatment making notes of any significant events. This information will be accessed by the study team and interrogated for AEs and SAEs and substantiated with information documented elsewhere in patients’ electronic health records. Compliance with the programme and adherence (or deviations) to the prescription will be monitored.

Intra-dialytic hypotension is common and affects 17% of all dialysis sessions [39]. We define IDH in accordance with the European Best Practice Guidelines [40] as a symptomatic drop in BP during dialysis of ≥ 20 mmHg in systolic or ≥ 10 mmHg in mean arterial pressures, requiring nursing interventions such as the stopping of ultrafiltration, administration of saline or moving patients to Trendelenburg position. IDH events are recorded in the nursing entries as above which will be used as a basis for coding this information.

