## Discussion

### Statement of novelty

We have proposed a novel and pragmatic study that simplifies incremental HD by focusing on key elements of patient welfare and safety using commonly used measures in the care of dialysis patients.

There is currently no agreement on the optimal method of implementing incremental HD and the term ‘incremental HD’ has been used variably in the past to describe twice-weekly treatment regimens of different aims and degrees of complexity [46–49]. In one version described by Kaja Kamal et al. [48], twice-weekly dialysis is administered on an ongoing basis as long as RRF is maintained above stdKt/V_urea_ > 2. This requires regular RRF measurements through timed urine collections and clinicians to react to changes in RRF and adjust dialysis prescriptions. Kaja Kamal et al. have previously reported that the patients spend a median of 9 months receiving incremental HD before transitioning to three-times weekly HD [48]. A trial of this regime is currently underway [50].

Our version of incremental HD is novel as we apply twice-weekly HD in a time-limited manner (i.e., the first 15 weeks of dialysis), which does not require time urine collections. In our regime, the key aim is to focus on reducing the risk of decompensation in the early days of dialysis, while patients are still adapting (and hence aiming to reduce the high rates of early mortality) which we hypothesise is related to intensity of dialysis [51]—our approach is in contrast to other therapy regimens [19, 46, 52] where the primary aim of treatment is to preserve RRF and hence influencing medium/long-term outcomes. Our regime is of a relatively short duration as we expect RRF to decline significantly [53, 54] in first few months of dialysis making twice-weekly HD unsustainable.

Other key features that distinguish this version of incremental HD from other solutions proposed previously[46, 50, 55, 56] include: simplified eligibility criteria (see Table 1) that pre-selects out-patient HD starters who are well prepared for dialysis; lack of adequate preparation [22, 57] significantly carry worse prognoses and such patients are not suitable for incremental HD. Note that previous studies have used more complex screening methods such as timed urine collections at baseline to select suitable candidates for incremental HD, but concerns have been voiced about completion and accuracy of urine collections in dialysis patients [58–60].

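### The historical control pool is not stated to meet the Table 1 restrictions placed on participants, so the descriptive safety comparison may favour incremental HD

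*Protocol article*

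**What the plan says.** **Intervention arm.** The Participants section and Table 1 (Protocol article) admit "Age ≥ 18 patients with CKD-5 who are about to start planned HD", in the out-patient setting, and require "At least 3 months of prior specialist renal follow-up at the time of starting HD". Exclusions include "Cross-over into HD from peritoneal dialysis" and a myocardial infarction within the previous 3 months. The reason given for the follow-up rule is: "Pre-dialysis specialist nephrology input for at least 3 months is essential since those without full preparation for dialysis may require intensive dialysis at presentation". Safety and adverse events data lists the planned-start rule as a safety measure, "we are only recruiting patient with planned out-patient dialysis start", and adds that it keeps out most people with critical complications.

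**Control arm.** Recruitment for control arm says: "Each participant in the incremental HD arm of the study will be matched with 2 patients who had previously received the conventional HD treatment". The source is described as follows: "All patients starting HD therapy since 2013, the inception date of the database, will be included in the searches". Having had conventional HD is the only condition stated.

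**Matching.** Matching method lists 14 propensity variables: age, CRP, albumin, access type, creatinine, dialysis facility, BMI, PTH, diastolic BP, haemoglobin, systolic BP, vitamin K antagonist use, cardiovascular history and antihypertensive treatment. Matching is 1:2 nearest neighbour, without a caliper and without replacement.

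**Use.** Secondary outcomes, part A, compares the two arms on AEs, SAEs, hospitalisations, 4p-MACE and all-cause mortality, among others. Analysis makes this descriptive, with no formal tests, and looks for potential signals.

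**The concern.** One arm is screened for being well prepared and clinically stable at dialysis start. The other, as written, is drawn from everyone who started. Late-referred patients, unplanned starters, transfers from peritoneal dialysis and people with a recent infarction could all be chosen as controls.

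The protocol supplies the likely direction. Statement of novelty says of inadequate preparation that it "significantly carry worse prognoses and such patients are not suitable for incremental HD". The same section makes historical controls acceptable only if key confounders are suitably matched. By the protocol's own account preparedness is such a confounder, yet it is neither a pool restriction nor a matching variable.

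At stake is the main reason given for having a control arm, which is to put safety event rates in context. If controls are sicker at the outset, a regimen with no benefit, or with some harm, could look as safe as conventional HD or safer. Study timeline and future plans says the data will be used to design the regimen for the later RCT. The absence of formal testing does not protect a descriptive contrast from selection bias.

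**Working it through.** **1. The plan's own figure.** 20 participants × 2 controls = 40, as in Sample size. This reproduces. There is no power calculation to check.

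**2. Restrictions set against the control specification.**

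| Restriction on participants | Stated for control pool? | Among the 14 variables? | Nearest proxy |
|---|---|---|---|
| Planned out-patient start | No | No | Access type, CRP, albumin |
| At least 3 months of nephrology care | No | No | Access type, albumin |
| No transfer from peritoneal dialysis | No | No | None evident |
| No infarction in preceding 3 months | No | No | Cardiovascular history (no time window) |

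The proxy column is my judgement; the other columns come from the text.

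**3. Size of a possible tilt, under no true effect.** The document gives no ineligible share and no event rates, so every input here is assumed. Let f be the share of *matched* controls who would fail Table 1, and r their event rate relative to eligible controls *after* matching.

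Inflation of the control rate = 1 + f(r − 1). Apparent ratio = 1 / [1 + f(r − 1)].

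- f = 0.2, r = 1.5: 1 + 0.2 × 0.5 = 1.10; ratio 0.91
- f = 0.3, r = 2: 1 + 0.3 × 1 = 1.30; ratio 0.77
- f = 0.4, r = 3: 1 + 0.4 × 2 = 1.80; ratio 0.56

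With a smaller share, f = 0.1 and r = 1.5, the ratio is 1/1.05 = 0.95.

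In counts, take an assumed 30% risk for eligible patients, f = 0.25 and r = 2. The control risk is 0.75 × 0.30 + 0.25 × 0.60 = 0.375. That is 15 expected events among 40 controls instead of 12, against 6 among 20 participants. The apparent ratio is 0.30/0.375 = 0.80.

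**4. Can matching on proxies remove it?** A small simulation used 20 eligible participants, a pool of 600, 1:2 nearest-neighbour propensity matching without caliper or replacement, 100 repetitions per setting, a base risk of 0.20 and r = 2. The proxies were catheter use (30% in eligible patients, 50% or 80% in ineligible) and a CRP-like marker half a standard deviation higher in ineligible patients.

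| Ineligible in pool | Catheter use if ineligible | Ineligible among matched controls | Apparent ratio |
|---|---|---|---|
| 20% | 50% | 19.5% | 0.84 |
| 20% | 80% | 16.1% | 0.86 |
| 40% | 50% | 35.4% | 0.74 |
| 40% | 80% | 29.1% | 0.77 |

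Restricting the pool first gave 0% ineligible and a ratio of 1.00 in all four settings. The simulation has two proxies where the plan has 14 variables, so the real matching could do better. It shows only that proxy matching need not clear the imbalance.

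**The case against.** **The search sentence may not be a selection rule.** It says who enters the searches, and a screen could follow. The same section calls these people participants for the control arm, Table 1 is headed as applying to study participants, and Fig. 1, which covers both groups, is not shown. A reader might infer that the plan sets out to use ineligible controls. The document does not support that. What stands is that the text runs from search to scoring with no screen between. Since the article already fixes source, covariates, algorithm, caliper and replacement, the eligible pool belongs to the same specification and is more than a detail left for elsewhere.

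**Matching and baseline reporting help.** The 14 variables were chosen because together they predict 2-year mortality in new starters. Access type, CRP, albumin and cardiovascular history plausibly track preparedness or acuity. Starting eGFR is to be reported for both arms, and the Charlson index and date of first nephrology contact are baseline items. This is fair: the tilt should be reduced, and some of it may be visible. It is not a reason to expect full removal.

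**The direction is not documented for every group.** The protocol speaks to poor preparation and unplanned starts. It gives no prognosis for transfers from peritoneal dialysis. It would also be too strong to say that every between-arm outcome is affected: albumin, haemoglobin and BP are themselves matching variables, and rate-ratio arithmetic does not apply to continuous measures.

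**Nothing decisive depends on it.** Recruitment is the primary outcome, and the feasibility thresholds (acceptance of at least 40%, retention of at least 70%) do not use controls. This stands, and it limits the severity.

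**Conclusion.** The point holds in moderate form. As written, controls are searched without the planned-start, nephrology follow-up, peritoneal dialysis and recent-infarction restrictions that define the intervention arm, and none of the 14 matching variables captures these directly. On the protocol's own statements about prognosis, the descriptive comparison of deaths, 4p-MACE, hospitalisations, AEs and SAEs may be tilted towards incremental HD.

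The documents do not support saying that the comparison *is* biased, or by how much. The 0.91–0.56 range depends wholly on assumed values of f (20–40% after matching) and r (1.5–3, after balancing the 14 variables); no single figure within it should be read as an estimate for this trial. If a screen is applied in practice, the problem is one of wording only. The primary outcome and the feasibility criteria are untouched. This should be fixed, but it does not invalidate the study.

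**What to change.** State that, before propensity scores are computed, the control pool is limited to patients who met, at HD start, the Table 1 criteria that records can show:

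- adult
- planned out-patient start
- at least 3 months since first nephrology contact
- no cross-over from peritoneal dialysis
- no myocardial infarction in the preceding 3 months

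Report the number excluded for each criterion. Consent, willingness and ability to comply cannot be applied to past records, so some difference between the arms will remain and should be acknowledged.

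The cost is a sentence in the plan and a filter on medical history that is already being extracted. The downside is a smaller matching pool. The target of 40 controls is unchanged if enough eligible patients remain, but the document does not give the pool size, so this should be checked first.

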#### Matching method

Propensity scores matching (PSM) will be undertaken to match participants in the incremental HD group with controls. Propensity scores will first be computed using logistic regression analysis accounting for the following 14 variables: age, C-reactive protein (CRP), serum albumin, vascular access type, pre-dialysis serum creatinine, dialysis facility, body mass index (BMI), parathyroid hormone levels (PTH), diastolic blood pressure (BP), haemoglobin, systolic BP, vitamin K antagonist treatment, history of cardiovascular disease and antihypertensive treatment. These variables together predict 2-year mortality in new dialysis starters with sensitivity and specificity of 72% and 69% based on a study by Siga et al. [24]. Matching will take place using the nearest neighbour method (no pre-specified caliper range) with no replacements.

### The intervention (the incremental HD regime)

Participants in the intervention group will receive incremental HD using a novel approach, starting therapy on twice-weekly basis with progressive increases in the duration and frequency of sessions over 15 weeks, achieving conventional treatment times by the end of this period.

The treatment delivered will comprise of a ‘start’ phase, representing just the first 2 days of dialysis (this is similar to conventional start), followed by 3 incremental phases or steps (also see Fig. 2):Start (phase 1): (first 2 days of HD): day 1, 2-h HD session; day 2, 3-h HD session.Phase 2: twice-weekly 2-h long dialysis sessions for 2 weeks.Phase 3: twice-weekly 3-h long dialysis session for 6 weeks.Phase 4: three-times weekly 3-h long session for 6 weeks.

Following this, participants will continue long-term HD as per clinical requirements. The regime includes several safety elements including frequent fluid status monitoring (through clinical examinations and bio-impedance analyses) and regular potassium testing. Clinicians and dialysis nurses can override the regime at any point if clinically indicated.

The regime tested here has been developed by the study investigators ([name], SB) in consultation with patient groups as a pragmatic way of reducing exposure to dialysis during the critical early transitional period. At the designing stage, patient engagement involved discussions with National Institute of Health Research (NIHR) patient research ambassadors for renal medicine at our centre and the members of Hull Kidney Patients Association (HKPA). In addition, a brief questionnaire was given out to 20 current HD patients to gauge their opinions on the current proposals. Patient feedback was very positive; patients particularly appreciated the focus on maintaining independence at the start of HD which they valued highly. HKPA members saw this as a much-needed advancement in dialysis therapies and felt that patients will be motivated to help. The group gave positive suggestions on how to narrow down the process of identifying potential participants e.g., by prioritising the sub-set of patients who were being referred for vascular access procedure (as they are the most likely patients to start dialysis soon). In the survey of 20 HD patients, 10 patients responded 7 of whom indicated that they would have taken part in the study if they had the opportunity.

### Sample size

As this is a feasibility study, a formal sample size calculation has not been performed. The recruitment target is 20 participants in the active interventional arm and 40 in the historical control group (1:2 matching).

### Follow-up

Participants will be followed-up for 6 months from the start date of HD therapy (see Fig. 1 above). A total of eight study visits will be carried out for each participant as per the schedule presented in supplementary table S1. Participant monitoring, and data collection is more intense in the first 2 weeks.

**Fig. 1 Fig1:**
[figure not shown]
Recruitment and follow-up of patients in the intervention and control groups

### Measurements and data items

#### Baseline data

Data items recorded at baseline include age, gender, primary renal disease, names of co-morbid conditions, medications list (including the names of anti-hypertensives and diuretics), date of first contact with nephrology services, type of vascular access and estimated glomerular filtration rate (eGFR) based on serum creatinine measurement prior to first dialysis session. Charlson co-morbidity index [25] will be calculated for all participants to enable baseline comparison of the burden of co-morbidities. With patients’ permission, we will cross-reference medication lists with their primary care records to ensure completion.

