### Recruitment

#### Recruitment for the intervention arm

Participants will be approached at the specialist pre-dialysis clinics or the dialysis unit with the participant information sheet (PIS). They will be given at least 24 h to consider the information. Following this, the investigator will meet patients in person to address their questions and obtain written informed consent if they show willingness to proceed. They will remain in-active in the study, and under follow-up with their usual care providers, until the decision is made to start HD by their caring physician. The timing of HD initiation will be made independently of the study investigators by the clinical care teams, based on clinical needs and in consultation with patients and their relatives. Clinicians will not be blind to patients’ participation in the study; some pre-dialysis CKD-5 patients may have already signed up for the study prior to commencing dialysis. Whether the knowledge of patients’ interest in incremental HD influences decisions about the timing of starting HD is not known. The starting eGFRs will be reported for both incremental and control arm patients which could help address this current knowledge gap.

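### The primary care completion of medication lists appears workable only for consented participants, so two of the 14 propensity-score variables may be measured differently by arm

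*Protocol article*

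**What the plan says.** Baseline data makes a medications list, with antihypertensives named, one of the items recorded at baseline. With the patient's permission the list is then checked against an outside source: "we will cross-reference medication lists with their primary care records to ensure completion". That sentence does not name an arm.

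Matching method fixes the covariates: "Propensity scores will first be computed using logistic regression analysis accounting for the following 14 variables". The list ends with "vitamin K antagonist treatment, history of cardiovascular disease and antihypertensive treatment", so two of the 14 are drug-treatment variables. The section does not say which version of the medication list supplies them.

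For the controls, the section on recruitment for the control arm says "Participants for the control arm will be identified using the local dialysis treatment database" and "All patients starting HD therapy since 2013, the inception date of the database, will be included in the searches". Their dialysis treatment data, "along with details of their medical history will be extracted for further analysis". It mentions neither permission nor primary care records. Consent is described only for the intervention arm, where "the investigator will meet patients in person to address their questions and obtain written informed consent".

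**The concern.** A propensity score balances what is recorded. If treatment status is recorded more completely in one arm, membership of that arm itself predicts being recorded as treated, and the logistic model absorbs this artefact into the score. A participant correctly recorded as untreated may then be paired with controls recorded as untreated because a prescription held in primary care never reached the local record. The balance table would not show it, because both of its columns use the same recorded values.

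At stake is how like-for-like the 20 participants and 40 controls are. The Discussion (Statement of novelty) says a control arm is needed to compare safety events and makes the historical-control strategy conditional on appropriate matching of key confounders. The Analysis section says the between-arm results will be examined for potential signals.

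**Working it through.** **Can the check be applied equally to both arms?**

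1. Nearest-neighbour matching needs a score for every candidate before any control is chosen. The candidate pool is all HD starters in the database since 2013.
2. A permission-based check that informs the score would therefore need permission from the whole pool. A check made only on the selected controls comes too late to change the matching.
3. Candidates who have died cannot give permission. The Introduction says mortality is highest in the first weeks of treatment, so completion among controls would depend on survival, and all-cause mortality is a listed secondary outcome.

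So either the check reaches the incremental arm only, or it reaches controls selectively. In both cases, using the completed list for matching means unequal measurement.

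**Inputs from the document.** 20 participants at 1:2 matching give 20 × 2 = 40 controls, which agrees with Sample size. Drug variables are 2 of 14, or 2/14 = 14% of the covariates.

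**Assumed inputs.** The document gives neither drug prevalence nor record completeness. Let p be true use in both arms, with p = 0.70 to 0.90 for antihypertensives. Let s be the share of true users captured by local records, with s = 0.80 to 0.95. Participants are taken as fully recorded, and no non-user is recorded as a user.

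**Formulas.**
- Truly treated among controls recorded as untreated: f = p(1 − s)/(1 − ps).
- If matching balances recorded use at p, true use among matched controls is p + (1 − p)f, so the hidden excess is (1 − p)f.

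**Results for antihypertensives.**

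| p | s | f | Hidden excess (1 − p)f | Of 40 controls |
|---|---|---|---|---|
| 0.70 | 0.95 | 0.035/0.335 = 0.104 | 0.30 × 0.104 = 0.031 | 1.3 |
| 0.70 | 0.80 | 0.140/0.440 = 0.318 | 0.30 × 0.318 = 0.095 | 3.8 |
| 0.80 | 0.90 | 0.080/0.280 = 0.286 | 0.20 × 0.286 = 0.057 | 2.3 |
| 0.90 | 0.95 | 0.045/0.145 = 0.310 | 0.10 × 0.310 = 0.031 | 1.2 |
| 0.90 | 0.80 | 0.180/0.280 = 0.643 | 0.10 × 0.643 = 0.064 | 2.6 |

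The range is about 3 to 10 percentage points, or 1 to 4 of 40 controls. At s = 1 the excess is zero.

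**Vitamin K antagonists.** Assuming 5-20% use and the same capture range, the excess runs from 0.95 × 0.0025/0.9525 = 0.002 to 0.80 × 0.040/0.840 = 0.038. That is 0.2 to 3.8 points, or 0.1 to 1.5 of 40.

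These figures treat each drug as if it were matched on its own. In a 14-variable score with no caliper, the effect of one item is diluted.

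**The case against.** The strongest reply is that the text does not establish the mismatch. Baseline data restricts the check to no arm. The Charlson index in the same paragraph "will be calculated for all participants to enable baseline comparison of the burden of co-morbidities", and the control-arm section also calls controls participants. Matching method does not say that the completed list feeds the score, which may already use local records in both arms. The article condenses a fuller protocol that is not shown, and no passage says local records are incomplete for these drugs. All of this stands. A reader might infer that the arms are definitely matched on differently measured covariates, but the document supports only a risk.

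A reader might also quote f, which reaches 64%, or the under-recording in the unmatched pool, p(1 − s), which reaches 0.90 × 0.20 = 18 points. Neither is the imbalance after matching. The 64% applies to a recorded-untreated group that, at p = 0.90, is only 4 of 40 controls.

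Nor can one say that the blood pressure, cardiovascular, hospitalisation and death comparisons are tilted in favour of incremental HD. Systolic and diastolic blood pressure and cardiovascular history are also in the score and may absorb part of the same severity, and the document gives no association between these drugs and the outcomes. More hidden disease among controls is plausible for the event outcomes. For blood pressure even the sign is unclear, since treatment itself lowers it.

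What the objection does not remove is the practical point. The text prescribes a permission-based completion of a variable that it also uses for matching against a retrospective pool, and it does not keep the two uses apart.

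**Conclusion.** The point holds as a conditional risk. If the primary-care-completed list supplies the two drug variables, they may be measured differently by arm, and their balance after matching may be partly apparent. For antihypertensives the hidden excess is about 3 to 10 percentage points (1 to 4 of 40 controls). This rests on the assumed 70-90% use and 80-95% local capture, on full recording in participants, and on matching on that drug alone. In the actual score it would be smaller, and with complete local records it would be zero.

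The reach is limited. The primary outcome is recruitment, and neither it nor the acceptance and retention thresholds use the controls. The between-arm comparisons are secondary and descriptive, without formal tests. This is a cheap improvement to the design and does not threaten the study's main conclusion.

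**What to change.** State in Matching method and in Baseline data that the medication variables used in the propensity score and in every between-arm baseline comparison come from the same source in both arms. That source should be the local dialysis and hospital record as it stood at the first HD session, before any primary care cross-check. Save that version of each participant's list before completing it, because the comparable version may be lost once the list is overwritten. Use the completed list only to describe the incremental arm, and label it so.

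The cost is about a sentence in each section and one saved copy of each list. The downside is that matching uses a slightly less complete medication list for participants.
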